#### **6.4.1 Specific criteria for withdrawal (if applicable):**

Not applicable

### **6.5 Replacement of individual subjects after withdrawal**

Not applicable

### **6.6 Follow-up of subjects withdrawn from treatment**

As we are measuring change over time and as there is no adverse effect to be expected subject who withdraw will not be followed on. They will be encouraged to contact us in case of any doubt.

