### **6.4 Withdrawal of individual subjects**

Subjects can leave the study at any time for any reason if they wish to do so without any consequences. The investigator can decide to withdraw a subject from the study for urgent medical reasons. Data collected from subject will be destroyed immediately.

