### 7.2 Adverse and serious adverse events

If any adverse or serious adverse event is to happen, subjects will be immediately informed, both by phone (this being faster) as in writing. They will then be given instruction to immediately stop using the trial products and if need be consult their physician, unless they require immediate medical attention in which case they will be instructed to report to the nearest emergency unit which will be updated by us on the condition and necessary treatment.

Adverse events are defined as any undesirable experience occurring to a subject during a clinical trial, whether or not considered related to the investigational drug. All adverse events reported spontaneously by the subject or observed by the investigator or his staff will be recorded.

A serious adverse event is any untoward medical occurrence or effect that at any dose results in death;

- is life threatening (at the time of the event);
- requires hospitalisation or prolongation of existing inpatients' hospitalisation;
- results in persistent or significant disability or incapacity;
- is a congenital anomaly or birth defect;
- is a new event of the trial likely to affect the safety of the subjects, such as an unexpected outcome of an adverse reaction, lack of efficacy of an IMP used for the treatment of a life threatening disease, major safety finding from a newly completed animal study, etc.

All SAEs will be reported to the accredited METC that approved the protocol, according to the requirements of that METC.

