##### **7.3 Follow-up of adverse events**

All adverse events will be followed until they have abated, or until a stable situation has been reached. Depending on the event, follow up may require additional tests or medical procedures as indicated, and/or referral to the general physician or a medical specialist.

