### **10.4 End of study report**

The investigator will notify the accredited METC of the end of the study within a period of 8 weeks. The end of the study is defined as the last patient's last visit.

In case the study is ended prematurely, the investigator will notify the accredited METC, including the reasons for the premature termination.

Within 18 months after the end of the study, the investigator/sponsor will submit a final study report with the results of the study, including any publications/abstracts of the study, to the accredited METC. Data collected will be kept for 5 years after termination of the

study after which they will be destroyed. This in case samples have to be re-analyzed.

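### Section 6.6 ends follow-up of withdrawn subjects with no exception for adverse events still open, which 7.3 requires to be followed, and 6.4 destroys their data without sparing the event record

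*Protocol*

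**What the plan says.** Five places in the Protocol bear on this point.

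- **6.6 (follow-up after withdrawal):** "As we are measuring change over time and as there is no adverse effect to be expected subject who withdraw will not be followed on". The only later contact it provides for is contact that the subject chooses to make.
- **7.3 (follow-up of adverse events):** "All adverse events will be followed until they have abated, or until a stable situation has been reached". It is not restricted to subjects still in the study, and it allows for extra tests and referral where the event calls for them.
- **6.4 (withdrawal):** "The investigator can decide to withdraw a subject from the study for urgent medical reasons". The next sentence reads: "Data collected from subject will be destroyed immediately".
- **7.2 (adverse events):** on recording, "All adverse events reported spontaneously by the subject or observed by the investigator or his staff will be recorded". On what subjects are told when an event occurs, "They will then be given instruction to immediately stop using the trial products and if need be consult their physician". Serious events go to the ethics committee.
- **10.4 (end of study report):** "Data collected will be kept for 5 years after termination" of the study. No exception is stated for withdrawn subjects.

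**The concern.** The subjects whose adverse events matter most for safety include those who leave because of one. For them the Protocol gives two instructions that do not fit together: stop following the subject (6.6), and follow the event to its end (7.3). A site that applies 6.6 as written would not learn the outcome of an event open at withdrawal. If a mild event later worsened or became serious, the site would hear of it only if the subject got in touch.

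The record has a problem of its own. Even if the event is followed, 6.4 does not keep what was written down before or after withdrawal. There is no data safety monitoring board (7.4), so the investigator's own follow-up and records carry the safety information. Section 6.7 relies on that information, because it ends the study if the products are believed to cause serious harm.

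**Working it through.** The point is textual and the Protocol gives no figure to reproduce. The check sets the rules side by side and looks for anything that reconciles them.

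**Step 1: scope of 6.6.** The operative words are "subject who withdraw will not be followed on". Two reasons are given. The first, that the study measures change over time, concerns the measurements and would suit a rule limited to study visits. The second, that no adverse effect is expected, is a safety reason. A rule justified partly by expected safety reads naturally as covering safety follow-up, and nothing in the sentence confines it to scheduled measurements.

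**Step 2: scope of 7.3.** It covers all adverse events, with no limit to subjects still taking part. A withdrawn subject with an open event is therefore inside both 6.6 and 7.3.

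**Step 3: whether a subject can fall under both.** There are two routes.

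- Under 6.4 the investigator may withdraw a subject for urgent medical reasons. An event can then be open at the moment of withdrawal. This is the firmer route.
- Under 7.2 subjects told of an event must stop the product. Section 7.2 does not call this withdrawal, but 6.6 is headed as covering withdrawal from treatment, so the rule can be read to apply.

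**Step 4: whether adverse effects are in fact foreseen.** The Summary mentions haematoma after blood sampling and, rarely, acute angle-closure glaucoma after pupil dilation. Section 5.4 mentions gastrointestinal complaints with omega-3. Section 6.3 includes a clinical safety profile in the blood tests. The second reason in 6.6 is therefore weak in general, and it fails outright for someone who withdraws because of an event.

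**Step 5: the record.** Section 6.4 orders destruction of the subject's data without qualification, directly after the sentence on medical withdrawal. Section 6.7, on early termination, limits destruction to measurement data, so narrower wording was available and is not used in 6.4. As written, 6.4 reaches the adverse-event record required by 7.2. It also does not fit the five-year retention in 10.4.

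**Step 6: search for a reconciling sentence.** Sections 6.7, 7.1, 7.4, 10.1, 10.3 and 10.4 contain none.

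**Step 7: how many subjects.** Inputs: five groups (Summary, study design), 20 per group and 10% dropout (4.4), and 100 subjects in total (4.1).

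- Total: 5 × 20 = 100.
- Withdrawals if the 10% dropout holds: 0.10 × 100 = 10.
- Of those, with an open adverse event: between 0 and 10. The Protocol gives no rate from which to narrow this.

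**The case against.** The best defence is that both sections can be obeyed. Section 7.3 is the specific safety rule and says all events. Section 6.6 is a general rule whose first reason concerns the measurements, so a site can stop scheduled visits and still follow an open event. The second reason in 6.6 describes the ordinary withdrawer. A subject with an open event does not meet that premise, so using 6.6 to cancel 7.3 stretches the text. This reading is possible and a careful site might adopt it. The Protocol does not say that 7.3 prevails, however, and 6.6 leaves later contact to the subject.

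On the record, serious events reach the ethics committee under 7.2 and appear in the annual report under 10.3, so the gravest information exists outside the subject's file. That stands, and it confines the loss mainly to non-serious events and to the later course of an event. The data to be destroyed in 6.4 might also mean measurement data only, but 6.4 does not say so and 6.7 does.

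The retention sentence in 10.4 is tied to possible re-analysis of samples, and a destruction rule for withdrawn subjects could be read as an exception to it. That is fair. The 10.4 mismatch is secondary, although its wording covers collected data in general.

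Finally, the range of 0 to 10 covers every possible value under the assumed dropout, so it shows no size of effect. That is correct, and the product is one egg or egg drink a day in healthy volunteers. The case rests on the rule being wrong as written and cheap to correct.

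**Conclusion.** The concern holds. Sections 6.6 and 7.3 give conflicting instructions for a subject who withdraws with an open adverse event, and 6.4 does not protect the record of that event. Followed literally, the stated rules lose safety information on subjects withdrawn for medical reasons.

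The size is modest. The number affected cannot be estimated from the Protocol and is probably small; the upper limit of 10 assumes that the 10% dropout in 4.4 holds. The duties in 7.2 to refer subjects for care and to report serious events are intact, so the gap is the later course, outcome and record of the event. The conflict between 6.6 and 7.3 has no bearing on the primary macular pigment analysis. This should be corrected. Confidence is medium, because a site could reasonably treat 7.3 as prevailing.

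**What to change.** 1. Limit 6.6 to the measurements: *Withdrawn subjects will have no further scheduled study measurements.*
2. Add to 6.6: *Adverse events open at withdrawal are followed under 7.3, subject to the subject's consent.*
3. Delete from 6.6 the expectation of no adverse effect as a reason for not following subjects.
4. Amend 6.4 so that adverse-event records and outcomes are exempt from immediate destruction and are kept for the period in 10.4.

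What care or tests the follow-up involves stays with the physicians, as 7.3 already provides.

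The cost is wording in 6.6 and 6.4, matching consent text on keeping adverse-event records, and a few extra contacts with subjects who leave with an open event. No extra subjects or scheduled procedures are needed.

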### **6.7 Premature termination of the study**

If for any reason we are to believe that the eggs or egg products are having serious adverse effects on the test subject, the study will be immediately terminated, however unlikely such an event may be. Our measurements involves proven techniques which

#### **Influence of modified eggs on macular pigment**

---

have already shown in many studies not to produce any SAE's, however, if such an event is to happen the study will also be terminated.

In either case test subjects will be informed in writing explaining the reasons for and possible action they need to take because of the serious adverse effects. All available measurement data will be destroyed, this in keeping with the subjects' anonymity.

## 7. SAFETY REPORTING

### 7.1 Section 10 WMO event

In accordance to section 10, subsection 1, of the WMO, the investigator will inform the subjects and the reviewing accredited METC if anything occurs, on the basis of which it appears that the disadvantages of participation may be significantly greater than was foreseen in the research proposal. The study will be suspended pending further review by the accredited METC, except insofar as suspension would jeopardise the subjects' health. The investigator will take care that all subjects are kept informed.

### 7.2 Adverse and serious adverse events

If any adverse or serious adverse event is to happen, subjects will be immediately informed, both by phone (this being faster) as in writing. They will then be given instruction to immediately stop using the trial products and if need be consult their physician, unless they require immediate medical attention in which case they will be instructed to report to the nearest emergency unit which will be updated by us on the condition and necessary treatment.

Adverse events are defined as any undesirable experience occurring to a subject during a clinical trial, whether or not considered related to the investigational drug. All adverse events reported spontaneously by the subject or observed by the investigator or his staff will be recorded.

A serious adverse event is any untoward medical occurrence or effect that at any dose results in death;

- is life threatening (at the time of the event);
- requires hospitalisation or prolongation of existing inpatients' hospitalisation;
- results in persistent or significant disability or incapacity;
- is a congenital anomaly or birth defect;
- is a new event of the trial likely to affect the safety of the subjects, such as an unexpected outcome of an adverse reaction, lack of efficacy of an IMP used for the treatment of a life threatening disease, major safety finding from a newly completed animal study, etc.

All SAEs will be reported to the accredited METC that approved the protocol, according to the requirements of that METC.

#### **Influence of modified eggs on macular pigment**

---

##### **7.3 Follow-up of adverse events**

All adverse events will be followed until they have abated, or until a stable situation has been reached. Depending on the event, follow up may require additional tests or medical procedures as indicated, and/or referral to the general physician or a medical specialist.

##### **7.4 Data Safety Monitoring Board (DSMB)**

Not applicable

## 8. STATISTICAL ANALYSIS

The statistical software package SPSS v15.0 en Stata/SE v8.2 will be used for data analysis. The students' T-test and ANOVA will be used to evaluate possible differences in continues variables between men and women, between subject with high and low fruit and vegetables intake en between subject with different iris colour.

The Chi-square test will be used to asses difference between baseline characteristics between groups (sex, iris colour, fruit and vegetable intake). If variables are not distributed normally they will be converted into Log-values.

In order to estimate changes in macular pigment optical density and retinal thickness over time, the General Linear Model (GML) will be applied for repeated measurements, with time as within subject factor and age, and iris colour as covariant.

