## 5. INVESTIGATIONAL MEDICINAL PRODUCT

Lutein, zeaxanthin and omega3 fatty acid are not medication but supplements. They are pro-vitamin and as such readily available at any drugstore. Furthermore, they are all naturally occurring supplements which are present in many vegetables (lutein and zeaxanthin) and fish (omega-3 fatty acid).

Testing shows the following concentrations for the eggs:

| In egg (mg/egg) | Lutein
Mg per egg yolk |          | Zeaxanthine
Mg per egg yolk |          |
|-----------------|---------------------------|----------|--------------------------------|----------|
|                 | mean                      | St dev   | mean                           | St dev   |
| Control         | 0,16778                   | 0,008655 | 0,08504                        | 0,001692 |
| Lutein          | 0,921422                  | 0,105767 | 0,137318                       | 0,013953 |
| Zeaxanthine     | 0,1743                    | 0,014454 | 0,487303                       | 0,031019 |

The omega-3 concentration is the same for all eggs and is  $200 \pm 10$ mg.

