#### 6.1.3 Other study parameters (if applicable)

Iris colour, diet, daily sun exposure time, alcohol consumption, anti cholesterol medication, vitamin supplement, and presence of intra ocular lens.

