#### **Questionnaire**

This is a short list of question regarding personal information, iris colour, refractory correction, diet, and lifestyle. This will be in Dutch. Subjects will also be asked to keep a nutrition diary. A nutrition diary will be filled for three days during the trial.

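### Section 8 reduces fruit and vegetable intake to high versus low in an exploratory comparison, losing power that a regression on graded intake would keep

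*Protocol*

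**What the plan says.** Section 8 states that the t-test and ANOVA "will be used to evaluate possible differences in continues variables between men and women", and the same sentence extends this to comparisons "between subject with high and low fruit and vegetables intake" and between iris colours. Intake is also a category in the baseline comparison: "The Chi-square test will be used to asses difference between baseline characteristics between groups (sex, iris colour, fruit and vegetable intake").

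Macular pigment optical density and retinal thickness over time get their own repeated-measures model, "with time as within subject factor and age, and iris colour as covariant". Intake is not in it.

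Section 6.1.3 places diet among the other study parameters: "Iris colour, diet, daily sun exposure time, alcohol consumption". The data come from two sources described in Section 6.3. For the questionnaire: "This is a short list of question regarding personal information, iris colour, refractory correction, diet, and lifestyle". For the diary: "A nutrition diary will be filled for three days during the trial". Section 3 puts one diary day at the start and two later. Section 5 describes the substances under test as "naturally occurring supplements which are present in many vegetables (lutein and zeaxanthin").

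The protocol gives neither a definition of high and low, nor a reason for using two levels, nor the response scale of the questionnaire's diet items.

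**The concern.** Sex and iris colour are categories by nature. Fruit and vegetable intake is not: a diary day can be turned into servings or grams. Cutting such a measure in two treats everyone on one side of the cut as alike and treats near neighbours on either side as different. A t-test on the halves is then less able to show a relation than a regression on the amounts.

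The protocol itself names vegetables as a source of lutein and zeaxanthin, so how background diet relates to measured values is a sensible thing to explore. Because the repeated-measures model leaves intake out, the high/low comparison is the only stated analysis that relates it to a continuous variable. At stake is the sensitivity of that one exploratory analysis. The two-level form is a method that the protocol states, not a detail that it leaves open.

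**Working it through.** **The plan's own figure.** The protocol gives no power or sample size for the intake comparison. Its only sample size (Section 4.4, Dutch text) reproduces: difference 9%, measurement error 7%, two-sided alpha 0.05/3 = 0.017, power 0.90. An exact two-sample t-test needs 18 per group (power 0.903; the normal approximation gives 17), and 18/0.9 = 20 after 10% dropout. Intake plays no part in it.

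**Inputs for the intake comparison**
- N = 100 (Section 4.1), and 100 × 0.9 = 90 with the 10% dropout of Section 4.4.
- Two levels, cut not stated (Section 8).
- Assumed, not in the documents: normal intake, linear relation, median cut, two-sided alpha 0.05, true correlation r of 0.20 to 0.40.

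**Information kept.** For a normal predictor cut so that a share p falls in the low group, with c = Φ⁻¹(p), the share of information kept is φ(c)²/[p(1 − p)]. At the median this is 0.3989²/0.25 = 2/π = 0.637. The loss is 36.3%, so 100 subjects carry the information of about 64.

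**Power.** Power = Φ(atanh(r)·√(N − 3) − 1.96), with r replaced by r·√(2/π) = 0.798r after the split. At r = 0.20 and N = 100:
- graded: 0.2027 × 9.849 − 1.96 = 0.037, power 51.5%;
- split: r = 0.1596, 0.1610 × 9.849 − 1.96 = −0.375, power 35.4%.

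| r | N = 100 graded | N = 100 split | N = 90 graded | N = 90 split |
|---|---|---|---|---|
| 0.20 | 51.5% | 35.4% | 47.2% | 32.3% |
| 0.25 | 71.1% | 51.2% | 66.4% | 47.0% |
| 0.30 | 86.2% | 67.2% | 82.3% | 62.4% |
| 0.40 | 98.7% | 90.3% | 97.7% | 87.0% |

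**Other cuts of a normal variable.** Loss is 38% at 40/60, 41% at one third/two thirds, 46% at 25/75, 51% at 20/80 and 66% at 10/90.

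**Other intake shapes, cut at the median, relation linear in intake.** Loss is 25% for uniform, 48% for lognormal with log-scale SD 0.5, 52% for exponential and 73% for lognormal with log-scale SD 1. Section 8 plans a log conversion for non-normal variables. If intake is lognormal and the relation is linear in log intake, the median cut separates the same subjects and the 36% figure applies again.

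**The median is not always the best cut.** For exponential intake the share kept at cut c is c²/(e^c − 1). At the median (c = 0.693) this is 0.480/1 = 48%. With 80% below the cut (c = 1.609) it is 2.590/4 = 65%.

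**The case against.** The strongest reply is that this is an exploratory comparison of subject characteristics. No objective concerns diet, Section 8 speaks of continuous variables without naming an endpoint, and the protocol never says that intake is recorded on a graded scale. The chi-square test fits an item answered in categories. If the answers come in a few ordered categories, less is lost than computed above; if they come in only two, that item loses nothing by being compared as two groups. All of this stands, and it sets the weight of the point. It does not remove it: the diaries are also planned and can yield amounts, and ordered categories would still support a trend analysis.

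Three stronger readings are tempting, and the documents do not support them.

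- A reader might infer that the split stays open to choice after the data are seen. A search over cuts would matter: in simulation with N = 100, a nominal 0.05 became about 0.12 for the best of three cuts, 0.16 for the best of five and 0.31 for the best between the 20th and 80th percentiles. But a cut point is commonly fixed in a statistical analysis plan, which is not at hand, so its absence here shows nothing.
- A reader might infer that the egg effect is put in doubt because vegetables compete as a lutein source. Groups are formed by lot (Section 6.2), and the high/low comparison neither estimates nor adjusts the contrast between them.
- A reader might take a loss of about a third as a fact of this trial. It is the result for one set of assumptions.

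**Conclusion.** The point holds as a minor one. The protocol commits to a two-level analysis of a variable for which it plans to collect data that can be graded, and that analysis is less powerful than the obvious alternative. The loss is about 36% of the information under normal intake, linearity and a median cut. That is 16 to 20 percentage points of power for correlations of 0.20 to 0.30 with 100 subjects. At the median it ranges from about 25% to 73% for the other shapes tried, and it is smaller if only ordered categories are recorded. The correlations are assumed too; at 0.40 the drop is about 8 points. The macular pigment model, the sample size and the egg contrast are untouched.

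**What to change.** In Section 8, replace the high/low t-test with a regression of each continuous variable on graded fruit and vegetable intake. Use the averaged diary amount, or the ordered questionnaire category scored as a trend. Adjust for randomised group wherever post-baseline values are used; two of the three diary days fall after the start, which is a further reason to do so. Keep any high/low table descriptive, at a cut fixed before the data are seen. The tests by sex and iris colour can stay as they are.

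This costs a few lines of wording and no new data. There are two small downsides. A linear or trend form must be assumed and checked, for example with a plot or a log scale. Three diary days also measure habitual intake with error, which weakens the graded analysis too; splitting does not remove that error.

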### Objective:

1. Assess any change in macular pigmentation due to lutein and zeaxanthin enriched egg consumption. Our hypothesis is that eggs are very effective at increasing macular pigment optical density by increasing the amount of lutein and zeaxanthin in the *macula lutea*.
2. Assessing changes in retinal morphology, visual acuity and contrast sensitivity. We will also analyze lipid profile in its relation to daily egg consumption.

This study uses some of measuring techniques mentioned in protocol id MEC 06-1-052 where tropicamide is also used and also measures macular pigment optical density.

**Study design:** Randomized placebo controlled interventional trial, where subjects divided into 5 groups, will be consuming either no eggs, normal eggs (lutein:  $0.168 \pm 0.08$ , zeaxanthin  $0.085 \pm 0.0017$ ), eggs enriched with lutein (lutein:  $0.921 \pm 0.106$ , zeaxanthin:  $0.137 \pm 0.014$ ), eggs enriched with zeaxanthin (lutein:  $0.174 \pm 0.014$ , zeaxanthin:  $0.487 \pm 0.031$ ), or egg product made from the lutein enriched eggs. The omega-3 concentration is the same for all eggs and is  $200 \pm 10$ mg. Subjects will pick up their test product (if applicable) at every control session and twice between every control session they will have to come to the Human Biology distribution department to receive additional products. The control group

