## 2. OBJECTIVES

Primary Objective: Assessing macular pigments' spatial distribution and the changes after consumption of modified eggs compared to normal eggs.

Secondary Objective(s): Assessing changes in retinal morphology, visual acuity and contrast sensitivity. We will also evaluate lipoprotein metabolism in relation to daily egg consumption.

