## 6. METHODS

### 6.1 Study parameters/endpoints

#### 6.1.1 Main study parameter/endpoint

Macular pigment optical density: the amount of measurable macular pigment in the macula region.

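### The Section 8 model for macular pigment has no randomised-group term, and no other stated analysis compares outcomes between the arms

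*Protocol*

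**What the plan says.** Section 8 of the protocol names three analyses:

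1. A t-test and ANOVA on continuous variables, with the comparisons listed as "between men and women, between subject with high and low fruit and vegetables intake en between subject with different iris colour".
2. A chi-square test of baseline characteristics between groups (sex, iris colour, diet).
3. A repeated-measures general linear model, introduced with the words "In order to estimate changes in macular pigment optical density and retinal thickness over time". It "will be applied for repeated measurements, with time as within subject factor and age, and iris colour as covariant".

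Only the third names the primary endpoint, which Section 6.1.1 defines as "Macular pigment optical density: the amount of measurable macular pigment in the macula region".

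Three other places set the question this model has to answer:

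- **Section 2:** the primary objective includes "the changes after consumption of modified eggs compared to normal eggs".
- **Summary, study design:** "Randomized placebo controlled interventional trial, where subjects divided into 5 groups". The groups are no eggs, normal eggs, lutein eggs, zeaxanthin eggs and an egg product made from the lutein eggs.
- **Section 4.4 (Dutch text):** three groups are to be compared with each other, with a Bonferroni level of 0.017, to detect a 9% difference in macular pigment.

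**The concern.** The objective, the randomisation and the Dutch sample-size text all point to a between-arm comparison. The model for the primary endpoint does not contain one. It lists its within-subject factor and its covariates, and leaves out the factor that was randomised.

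A time effect without a comparator cannot separate an egg effect from anything else that moves between Day 1 and Day 90, such as season, diet, instrument drift or, for some instruments, practice. Section 6.2 states that there is no blinding, and the flicker photometry in Section 6.3 depends on the subject's button press, so expectation or learning could shift readings in every arm. Only a contrast between arms removes a shift that all arms share. With five arms and no named contrast, the choice of comparison also stays open until the data have been seen.

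**Working it through.** **1. What the sample size assumes.** Inputs from the Dutch text of Section 4.4: difference 9%, measurement error 7% (taken as the SD), alpha 0.017, power 0.90. Two-sided testing is assumed, because the text does not say.

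- Normal approximation: n = 2 × [7 × (2.387 + 1.282) / 9]² = 16.3, so 17 per group.
- Exact two-sample t-test: power is 88.3% at 17 and 90.4% at 18, so 18 per group.
- Dropout: 18 / 0.9 = 20 per group, and 5 × 20 = 100, the total in Section 4.1.

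The stated 18 is therefore reproduced as a pairwise between-group comparison.

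The English note in the same section uses 11.7% and alpha 0.05. For two samples these give 2 × [11.7 × (1.960 + 1.282) / 9]² = 35.5, so 36 per group (37 by exact t). They give 18 only as a one-sample or paired change by the normal approximation (17.8; 20 by exact t). The two texts need reconciling, but the Dutch one states the between-group aim in words.

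**2. Which stated analysis makes that comparison.**

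| Section 8 analysis | Outcome | Compared by | Randomised arm? |
|---|---|---|---|
| t-test / ANOVA | continuous variables (could include MPOD) | sex, fruit and vegetable intake, iris colour | no |
| Chi-square | baseline characteristics | groups | yes, but baseline only |
| Repeated-measures model | MPOD, retinal thickness | time; age and iris colour as covariates | no |

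None does, and no other section adds one.

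**3. Size of the problem, as an illustration.** Assumptions: 90 evaluable subjects (5 × 18), a one-sample test of the Day 1 to Day 90 change, two-sided 0.05, covariates and the Day 45 visit ignored, no egg effect, and the same drift d in every arm. The noncentrality is d / (SD / √90). The documents give no SD of change, so a range is shown: 7 × √2 = 9.9; 11.7; and 11.7 × √2 = 16.5.

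| SD of change | noncentrality at d = 3% | P(significant), d = 3% | P(significant), d = 2% |
|---|---|---|---|
| 9.9% | 3 / 1.044 = 2.87 | 81% | 47% |
| 11.7% | 3 / 1.233 = 2.43 | 67% | 36% |
| 16.5% | 3 / 1.739 = 1.72 | 40% | 21% |

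A between-arm test has no noncentrality here, because the drift cancels. Its rate is the nominal 5% (4.9% in a simulation at SD 9.9%, 18 per arm, 3% drift).

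If the model is run within each arm instead, √90 becomes √18. The noncentrality at 3% drift falls to 1.29, 1.09 and 0.77, and the rates to about 23%, 18% and 11% per arm. These are lower but still above 5%, and there is still no test between arms.

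**4. When eggs do work.** If the three enriched arms rise 9% and the other two 0%, the pooled change is 9 × 3/5 = 5.4%, a value true in no arm. If only one arm rises 9% (SD 9.9%, 18 per arm, simulated), the pooled time test is significant in about 36% of trials and a between-arm ANOVA in about 77%.

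**The case against.** The strongest reply is that the comparison is plainly intended. Section 2 states it, the Dutch text of Section 4.4 is sized for it, and the full list of model terms is often left to an analysis plan, which may exist. This stands as far as intent goes. A reader might infer that the investigators mean to pool all subjects and never compare the arms, and the documents do not support that: Section 8 nowhere says subjects are pooled. The reply does not cure the text, because Section 8 is not silent on the model. It writes the terms out and omits the randomised one, so the stated model conflicts with the stated objective.

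A second reply is that MPOD is a continuous variable and so falls under the t-test and ANOVA. That is fair, and the repeated-measures model should not be called the only analysis that could touch MPOD. But the comparisons listed there are by sex, diet and iris colour.

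A third concerns the illustration. No drift of 2% or 3% is sourced in the protocol, the SD of change is assumed, and a one-sample test simplifies a three-visit model. Practice effects are also implausible for the reflectometer, the instrument named in the Dutch sample-size text: Section 6.3 says the subject is unaware of the recording. All of this limits the figures. It does not change their direction.

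**Conclusion.** The point holds. Section 8 omits randomised group and group-by-time from the model for the primary endpoint, contrary to Section 2 and to the between-group sample size with Bonferroni 0.017 in Section 4.4. As written, pooled or by arm, the model cannot answer the primary question. That follows from the text alone and needs no numerical assumption.

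The size does need assumptions. For a common 3% drift with no egg effect, the pooled test is significant in 40% to 81% of trials over SDs of change from 16.5% down to 9.9%, against 5% for a between-arm test. A reader might take 81% as this trial's false-positive rate. It is not: it is the value at the smallest of three assumed SDs and at a drift the protocol does not report.

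This should be corrected before analysis, since it concerns the main endpoint and the central contrast of the trial.

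**What to change.** In Section 8:

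- Add randomised group (five levels, between subjects) and group-by-visit to the repeated-measures model.
- Define the primary analysis as three Day 90 contrasts: lutein egg, zeaxanthin egg and egg product, each versus normal eggs, adjusted for Day 1 MPOD, age and iris colour. With Day 1 as a covariate, the repeated outcomes are Days 45 and 90.
- Test these three contrasts at 0.05 / 3 = 0.017, the level already in Section 4.4. An overall five-group test is a different test and should not be named as primary beside them.
- Treat comparisons with the no-egg arm as secondary. The Summary uses the term control group both for subjects adding no eggs and for those given conventional eggs, so state that normal eggs are the primary comparator, as in Section 2.

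In Section 4.4, reconcile the three groups with the five arms, and align the Dutch text and the English note.

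The cost is rewording Section 8 and a short correction to Section 4.4 and the Summary. No new data or visits are needed. On the Dutch inputs, 18 per group is already sized for a pairwise comparison at 0.017, so that figure does not change for this reason.
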